#### Missing Data

As the only certain way to avoid biases from missing data is to collect complete data [152], the study team will strive to minimize missing observations by using study procedures that reduce participant burden. Participants who experience difficulties completing assessments on the web will have the option to complete assessments on paper or over the telephone with the research staff. Participants with time constraints or other barriers to completing outcome assessments will be given the option to complete only the primary outcome, that is, the HADS scale. Participants who withdraw from treatments will be encouraged to continue completing the outcome assessments. Reasons for withdrawal will be recorded for those who completely withdraw from the study. Given that missing data are inevitable in a prospective study, sensitivity analyses will be performed to assess the impact on the results of adjusting for patient disease progression or death, and analytical strategies that are as robust as possible to data losses will be applied. The study team will first explore whether missingness is associated with observed variables (eg, randomization arm and baseline outcome measures) by comparing patients with complete and incomplete data. Notably, the LMMs described previously will include patients with incomplete data under the missing at random assumption. However, the exploration of the data may deem the missing at random assumption to be inappropriate. Multiple imputation and pattern mixture models are well-established methods for addressing these issues [153,154]. Sensitivity analyses will be performed to evaluate the robustness of the LMM results by refitting the models after imputing the missing week 8 and week 26 outcomes using multiple imputation.

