#### Aim 1—Hypotheses 1(a) and 1(b)

Outcome measure trajectories will be plotted by randomization arm over time. Each outcome measure will be summarized at each assessment time by treatment arm using descriptive statistics. Comparisons between randomization arms with respect to changes in symptom outcomes will be based on specific coefficients from time-by-arm interactions added to the general LMM template described above in the *General Description* section. Specifically, the model will include all time points (categorical) at which the outcome was assessed (baseline and weeks 4, 8, 16, and 26), and the time-by-arm interaction will include multiple coefficients corresponding to the time-by-arm interaction at each discrete postbaseline time point. However, statistical inferences will focus on the interaction coefficients at 8 and 26 weeks, which are interpreted as the differences between arms in change from baseline to 8 and 26 weeks, respectively. For hypothesis 1(a), the 2 primary end points are HADS anxiety score changes at 8 weeks and 26 weeks. On the basis of the LMM coefficients for the time-by-arm interaction at weeks 8 and 26, 2 tests will be performed to determine whether MT is noninferior to CBT at reducing the HADS anxiety subscale score within a noninferiority margin of 0.35 SD for both comparisons. The noninferiority of MT to CBT will be tested at a significance threshold of *P*<.025 for each comparison, controlling the overall type I error at *P*=.05 for the primary end point comparisons. For hypothesis 1(b), a similar LMM evaluating BFI scores over time will be used to test whether the MT arm had significantly greater improvement in fatigue (BFI score) compared with the CBT arm at weeks 8 and 26. In contrast to the primary end point noninferiority comparisons, these tests will be superiority tests. For other comorbid symptoms (eg, depression and insomnia) and quality of life, the methods described for hypothesis 1(b) will be used to compare the treatment arms. Given that a small number of cancer survivors may experience disease recurrence during the 26-week study, sensitivity analyses will be performed, excluding those individuals who experienced a recurrence during the study period. These sensitivity analyses will not replace the primary analysis.

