#### Sample Size and Power

The sample size is based on the primary hypothesis that MT is noninferior to CBT for anxiety reduction at weeks 8 and 26. Two tests will be performed to determine whether MT is noninferior to CBT at reducing HADS anxiety at weeks 8 and 26, each with a noninferiority margin of Cohen *d*=0.35 SD for both comparisons. These comparisons will be based on the LMM coefficients for the time-by-arm interaction at weeks 8 and 26; however, the power calculation is based on 2-sample *t* tests of differences between the arms in their change scores. Therefore, the power estimate is conservative, that is, in the LMM-based analysis, there will be slightly higher power than the power calculation presented below, with all other assumptions held constant. Assuming 150 participants are randomized to each arm, 15% attrition, and a 1-sided significance threshold of *P*=.025 (controlling the overall type I error at 0.05 for our 2 primary end point comparisons), there will be 80% power to find MT noninferior to CBT with respect to the HADS anxiety subscale scores at weeks 8 and 26 within a noninferiority margin of Cohen *d*=0.35 SD.

The noninferiority margin was informed by a large study that used multiple rigorous methods to empirically estimate a difference of 1.7 points as the MCID for the HADS scales [120]. In preliminary data from CBT recipients with baseline HADS anxiety subscale scores ≥8, the SD for the HADS anxiety subscale score was 4.2 at week 8 [110]. In addition, in a large acupuncture trial of cancer survivors, among 159 patients with baseline HADS anxiety subscale scores ≥8, the HADS anxiety subscale score SD was 4.0 during follow-up [155,156]. On the basis of these studies, it is assumed that the HADS anxiety subscale score SD will be approximately 4.2. Dividing the raw-score MCID of 1.7 points by 4.2 yields a standardized difference, that is, Cohen *d*=0.40. The noninferiority margin of Cohen *d*=0.35 SD is smaller than the standardized MCID (Cohen *d*=0.40) of the HADS anxiety subscale; as such, the noninferiority margin and statistical approach will find MT to be noninferior to CBT only if MT is not meaningfully worse than CBT.

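### The multiple imputation offered as the missing-data check makes, as described, the same missing-at-random assumption as the LMM, so agreement between them says little about informative dropout

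*Protocol article*

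**What the plan says.** The Missing Data section of the protocol article makes four statements in sequence.

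1. On the main analysis: "the LMMs described previously will include patients with incomplete data under the missing at random assumption".
2. After a planned comparison of participants with complete and incomplete data (arm and baseline outcome are the examples given), it warns that "the exploration of the data may deem the missing at random assumption to be inappropriate".
3. On the remedy: "Multiple imputation and pattern mixture models are well-established methods for addressing these issues".
4. On what will be done to judge robustness: "refitting the models after imputing the missing week 8 and week 26 outcomes using multiple imputation".

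Two other sensitivity analyses bear on incomplete follow-up. In the same section, "sensitivity analyses will be performed to assess the impact on the results of adjusting for patient disease progression or death". Under Aim 1, "sensitivity analyses will be performed, excluding those individuals who experienced a recurrence during the study period".

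The result to be protected is the pair of noninferiority tests on HADS anxiety at weeks 8 and 26, each "within a noninferiority margin of 0.35 SD for both comparisons". Under Sample Size and Power, "it is assumed that the HADS anxiety subscale score SD will be approximately 4.2".

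**The concern.** A sensitivity analysis for missing data is useful when it changes the assumption about the values that were not seen. Multiple imputation with no stated shift or reference rule draws those values from a model fitted to the observed data, which is the MAR assumption again. If dropout depends on the unseen anxiety score, the LMM and the imputation are wrong together and by nearly the same amount. Their agreement would then be read as robustness.

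The lead-in has a related fault. It implies that exploring the data can show MAR to be inappropriate. Missingness related to arm or baseline is compatible with MAR, and the LMM already contains both (arm as a factor, baseline as a modelled time point). Dependence on unseen scores cannot be detected by comparing seen ones.

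The method that could depart from MAR, the pattern mixture model, is named in the third statement and dropped in the fourth. The progression/death and recurrence analyses, as stated, do not vary the assumption about unseen HADS scores. At stake is a conclusion that MT is noninferior, supported by a check that could not have warned against it.

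**Working it through.** **Inputs.** From Sample Size and Power: 150 per arm, 15% attrition (150 × 0.85 = 127.5 evaluable), one-sided 0.025 per test, margin 0.35 SD, SD 4.2. Margin in points: 0.35 × 4.2 = 1.47. The SD is applied to the change score, because the plan's power calculation compares change scores.

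**The plan's own figure.** Standard error in SD units = √(2/127.5) = 0.1252. Power at a true difference of 0 = Φ(0.35/0.1252 − 1.96) = Φ(0.835) = 79.8% (79.5% with the noncentral t). The stated 80% reproduces and is not in question.

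**Does standard imputation add information?** A simulation of 1,500 trials used 150 per arm, SD 4.2, within-person correlation 0.6 (assumed), 15% missing at week 26, and a true MT disadvantage equal to the margin, 1.47. It compared a MAR likelihood estimate (saturated, standing in for the random-intercept LMM) with standard multiple imputation.

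| Dropout | Truth | MAR likelihood | Multiple imputation |
|---|---|---|---|
| Unrelated to outcome | 1.47 | 1.47 | 1.47 |
| In MT, depends on the unseen week 26 score | 1.47 | 1.04 | 1.04 |

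In the second row both methods are biased by 1.47 − 1.04 = 0.43 points toward noninferiority. Within a run they differ by only about 0.03 points on average, as they also do when nothing is wrong.

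**How large could the error be?** Let the missing participants be worse than the MAR prediction by δ points (δ_MT and δ_CBT), with 15% missing in each arm. Then:

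- bias toward noninferiority = 0.15 × (δ_MT − δ_CBT);
- standard error = 4.2 × √(2/127.5) = 0.526 points;
- per-test one-sided error with the true difference at the margin = 1 − Φ(1.96 − bias/0.526).

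With the shift in MT only (δ_CBT = 0):

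| δ_MT (assumed) | Bias | Share of 1.47 | One-sided error |
|---|---|---|---|
| 0 | 0 | 0% | 0.025 |
| 1 | 0.15 | 10% | 1 − Φ(1.675) = 0.047 |
| 2 | 0.30 | 20% | 1 − Φ(1.390) = 0.082 |
| 3 | 0.45 | 31% | 1 − Φ(1.104) = 0.135 |

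The other cases follow from the same formulas. Equal shifts in both arms give zero bias. A shift in CBT only works against noninferiority. For example, with δ_CBT = 2 and truly equal treatments, the MAR estimate is 0.30 points against MT, and power falls to Φ((1.47 − 0.30)/0.526 − 1.96) = Φ(0.264) = 60%.

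**Tipping point.** With an observed difference of 0, the upper limit is 1.96 × 0.526 = 1.03 points, leaving 1.47 − 1.03 = 0.44 of room. An MT-only shift of 0.44/0.15, about 2.9 points, moves the limit to the margin.

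**The case against.** The strongest reply is that the article attaches MAR explicitly only to the LMM and gives no imputation model. Multiple imputation can be run under other assumptions, including a delta shift, and the article names pattern mixture models. A statistical analysis plan may exist, and imputation models, shift ranges and tipping points are commonly left to it. This limits the point. It concerns imputation as described here, not every form of it, and the absence of a delta grid from a journal article is not itself the fault. What stands is the text's own sequence: it doubts MAR, then commits to a check that on its ordinary reading assumes MAR.

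Three stronger readings are tempting and are not supported.

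- *That the plan is biased toward noninferiority.* The direction is unknown. The table above shifts MT only, by assumption. The one dropout worry the article raises concerns the comparator: the Introduction cites 20% to 25% not completing CBT, which is treatment non-completion and not missing outcomes.
- *That MAR credits MT dropouts with the benefit of those who stayed.* The LMM conditions on each participant's own earlier scores, and there are five assessments, so a poor early response carries into the prediction. Only the part of the unseen score that earlier scores do not predict is at issue.
- *That data exploration decides which analysis is run.* No such rule exists. The imputation is unconditional, and the fault is one sentence that overstates what exploration can show.

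The plan also works to limit missing data: telephone or paper completion, a HADS-only option, and continued assessment after treatment withdrawal. These reduce the amount missing. They do not test the assumption about what remains.

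**Conclusion.** The point holds in a limited form and should be acted on. As described, the imputation of weeks 8 and 26 shares the MAR assumption of the LMM, so agreement between the two is weak evidence against informative dropout. The analysis that could provide such evidence is named but not committed to.

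The illustrated size is a bias of 0.15 to 0.45 points on a 1.47-point margin, and a per-test one-sided error of 0.047 to 0.135 instead of 0.025. This rests on assumed shifts of 1 to 3 points beyond the MAR prediction in MT only, on the planning attrition of 15% applying at the tested week, and on SD 4.2. The 2- and 3-point shifts exceed the cited minimal clinically important difference of 1.7 points, so they are demanding cases. The figures show what the check could miss and do not predict what will happen. The stated power and sample size are unaffected.

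**What to change.** Keep the MAR imputation and treat it as the case δ = 0. Add a prespecified delta-adjusted pattern-mixture analysis at weeks 8 and 26:

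- Impute within arm, add δ_MT and δ_CBT to the imputed HADS anxiety values, and refit the model.
- Vary the two shifts separately over a grid fixed in advance, for example 0 to 4 points in steps of 0.5. Include MT shifted with CBT unshifted.
- Report, for each week, the combinations at which the upper confidence limit crosses the 0.35 SD margin, so that readers can judge whether they are plausible.

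Reword the sentence on data exploration so that the comparison of complete and incomplete cases describes missingness patterns and is not presented as a judgement on MAR. If the statistical analysis plan already contains such an analysis, it is enough to say so here.

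The cost is a few hours of programming on an imputation already planned, with no new data and no change to the primary analysis or sample size. The downside is that the result may look less robust. The grid should be fixed before outcomes are seen by arm.

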#### Sample Size and Power

The sample size is based on the primary hypothesis that MT is noninferior to CBT for anxiety reduction at weeks 8 and 26. Two tests will be performed to determine whether MT is noninferior to CBT at reducing HADS anxiety at weeks 8 and 26, each with a noninferiority margin of Cohen *d*=0.35 SD for both comparisons. These comparisons will be based on the LMM coefficients for the time-by-arm interaction at weeks 8 and 26; however, the power calculation is based on 2-sample *t* tests of differences between the arms in their change scores. Therefore, the power estimate is conservative, that is, in the LMM-based analysis, there will be slightly higher power than the power calculation presented below, with all other assumptions held constant. Assuming 150 participants are randomized to each arm, 15% attrition, and a 1-sided significance threshold of *P*=.025 (controlling the overall type I error at 0.05 for our 2 primary end point comparisons), there will be 80% power to find MT noninferior to CBT with respect to the HADS anxiety subscale scores at weeks 8 and 26 within a noninferiority margin of Cohen *d*=0.35 SD.

The noninferiority margin was informed by a large study that used multiple rigorous methods to empirically estimate a difference of 1.7 points as the MCID for the HADS scales [120]. In preliminary data from CBT recipients with baseline HADS anxiety subscale scores ≥8, the SD for the HADS anxiety subscale score was 4.2 at week 8 [110]. In addition, in a large acupuncture trial of cancer survivors, among 159 patients with baseline HADS anxiety subscale scores ≥8, the HADS anxiety subscale score SD was 4.0 during follow-up [155,156]. On the basis of these studies, it is assumed that the HADS anxiety subscale score SD will be approximately 4.2. Dividing the raw-score MCID of 1.7 points by 4.2 yields a standardized difference, that is, Cohen *d*=0.40. The noninferiority margin of Cohen *d*=0.35 SD is smaller than the standardized MCID (Cohen *d*=0.40) of the HADS anxiety subscale; as such, the noninferiority margin and statistical approach will find MT to be noninferior to CBT only if MT is not meaningfully worse than CBT.

Regarding the sample size for the qualitative analyses, the number of participants required to draw meaningful conclusions from semistructured interviews is determined by saturation, that is, the point at which existing themes are fully understood and no new themes emerge through further data collection [157]. Prior research has indicated that thematic saturation can typically be obtained with <15 interview participants, although these findings were based on relatively homogeneous samples [158]. Given that this study is enrolling a more heterogeneous population, the plan is to conduct 30 interviews in each treatment arm to better capture the diverse perspectives.

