### The Music Therapy Versus Cognitive Behavioral Therapy for Cancer-Related Anxiety Trial: Study Aims and Hypotheses

The Music Therapy Versus Cognitive Behavioral Therapy for Cancer-related Anxiety (MELODY) trial seeks to address the following aims:

The primary aim is to determine the comparative effectiveness of telehealth-based MT versus telehealth-based CBT for anxiety and comorbid symptoms in cancer survivors.

*Hypothesis 1(a)*: MT will be noninferior to CBT in treating anxiety symptoms among survivors at week 8 (end of treatment) and week 26 (long-term follow-up).*Hypothesis 1(b)*: Compared with CBT, MT will be associated with significantly greater improvement in fatigue co-occurring with anxiety.Exploratory hypothesis: Survivors may have unique experiences with MT and CBT for anxiety during cancer survivorship.

The secondary aim is to identify patient-level factors associated with greater anxiety symptom reduction after MT and CBT.

*Hypothesis 2*: Specific sociodemographic characteristics (eg, age, sex, race, and education) or psychological attributes (ie, expectancy) will be associated with treatment response to MT or CBT.

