### Randomization

After completing the baseline assessments, participants will be randomized using MSK’s secure computer system that ensures full allocation concealment. Randomization will be 1:1 (MT:CBT) using randomly permuted blocks of random length, which are stratified by study site, current anxiety medication use (yes or no), and preferred language (English or Spanish). The principal investigator and biostatistician will be blinded to treatment assignments.

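### The 80% power stated for noninferiority at weeks 8 and 26 is the power of one comparison; the success rule for Hypothesis 1(a) is not fixed, and power for both weeks together is about 66–72%

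*Protocol article*

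**What the plan says.** - **Study Aims and Hypotheses.** Hypothesis 1(a) is a single statement covering two time points: "MT will be noninferior to CBT in treating anxiety symptoms among survivors at week 8 (end of treatment) and week 26 (long-term follow-up").
- **Aim 1—Hypotheses 1(a) and 1(b).** The analysis section treats the time points as two end points: "the 2 primary end points are HADS anxiety score changes at 8 weeks and 26 weeks". Two noninferiority tests are planned, with a threshold of 0.025 "for each comparison, controlling the overall type I error at *P*=.05 for the primary end point comparisons".
- **Sample Size and Power.** The sample size is tied to the primary hypothesis, in the singular. The calculation takes 150 people per arm, loses 15% of them, sets a margin of 0.35 SD at each week and uses two-sample t tests on change scores. Its error level is "a 1-sided significance threshold of *P*=.025 (controlling the overall type I error at 0.05 for our 2 primary end point comparisons"). The conclusion is that "there will be 80% power to find MT noninferior to CBT with respect to the HADS anxiety subscale scores at weeks 8 and 26".

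The article does not say whether Hypothesis 1(a) is supported when only one of the two tests succeeds. It also does not say whether the 80% applies to each test or to both together.

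**The concern.** The hypothesis and the power sentence join the two weeks with an *and*. Taken at face value, they promise an 80% chance of showing noninferiority at both. The alpha rule describes something else: dividing 0.05 between two tests is needed only when success at either week can be claimed by itself. If both must succeed, requiring both already controls the error, and no division is called for.

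Two things are at stake. A reader may take 80% as the chance of supporting the whole primary hypothesis, which the design does not have with these tests. And a split result, with noninferiority shown at one week only, is a realistic outcome. The text as it stands would let that result be called support or non-support after the data are seen.

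**Working it through.** **Inputs from the article.** 150 randomized per arm, 15% attrition, margin 0.35 SD and one-sided 0.025 per test (Sample Size and Power); 1:1 allocation (Randomization). The SD of 4.2 points cancels because the margin is in SD units.

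**Assumptions not in the article.** True difference of zero at both weeks, the same number evaluable at both weeks, and a correlation ρ between the week 8 and week 26 test statistics, varied from 0 to 0.9.

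**Step 1: reproduce the stated 80%.**
- Evaluable per arm: 150 × 0.85 = 127.5; degrees of freedom 2 × 127.5 − 2 = 253.
- Noncentrality: 0.35 × √(127.5/2) = 2.795.
- Noncentral t power at one-sided 0.025: 79.5%. The normal approximation gives 79.8%.

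The stated 80% is therefore the power of **one** test.

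**Step 2: power for both weeks, and for at least one, with the same tests.** Put b = Φ⁻¹(0.795) = 0.824. Joint power is P(Z₁ < b, Z₂ < b) for a bivariate standard normal with correlation ρ. Power for at least one week is 2 × 0.795 − joint. The chance that exactly one week succeeds is 2 × (0.795 − joint).

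| ρ | both weeks | at least one | exactly one |
|---|---|---|---|
| 0 | 0.63 | 0.96 | 0.33 |
| 0.3 | 0.66 | 0.93 | 0.27 |
| 0.5 | 0.68 | 0.91 | 0.23 |
| 0.7 | 0.71 | 0.88 | 0.18 |
| 0.8 | 0.72 | 0.87 | 0.14 |
| 0.9 | 0.74 | 0.85 | 0.10 |

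At every correlation shown, 80% is neither the joint power nor the power for at least one success. Joint power equals the single-test figure only at ρ = 1.

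**Step 3: what the alpha split does.** With the true difference at the margin at both weeks, the chance of at least one false claim from two one-sided 0.025 tests is 1 − P(Z₁ < 1.96, Z₂ < 1.96). This is 0.049 at ρ = 0, 0.048 at 0.3, 0.045 at 0.5, 0.042 at 0.7 and 0.039 at 0.8. All are within the declared 0.05, so the split is right for separate claims.

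**Step 4: both weeks required, no split.** If both tests must succeed, one-sided 0.05 at each week already holds the overall error at 0.05. Single-test power is then 87.3%, and joint power is 0.778, 0.792, 0.810 and 0.821 for ρ = 0.3, 0.5, 0.7 and 0.8.

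**The case against.** The strongest reply is that nothing is wrong with the design. The operative statistical text names two primary end points, plans two tests and sets a threshold for each comparison. On that reading the split, the overall 0.05 and 80% per test fit together, and the 80% reproduces. The *and* in the hypothesis is then ordinary prose listing two time points. How two end points combine into one conclusion may also be set out in the full protocol or analysis plan, which is not shown.

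Much of this stands. A reader might infer that Hypothesis 1(a) *requires* success at both weeks and that the trial is therefore underpowered. The article does not support that, because it nowhere sets such a rule. A reader might also object that an overall one-sided error near 0.05 is too lenient for a noninferiority claim. But the article declares 0.05 openly and the tests stay within it, so this is a design choice and not an error. Nor does a both-weeks rule by itself bring power down to 66–72%: that figure applies only if 0.025 per test is kept, and Step 4 shows about 78–82% without the split.

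The figures are also conditional on an assumed correlation. The article says the mixed model will have slightly more power than the t test; that gain is not quantified and is not credited here.

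What the reply does not remove is the wording of the power sentence. It attaches 80% to the two weeks together, directly after tying the sample size to one hypothesis covering both. This is a matter of what the article states, not of detail left to another document.

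**Conclusion.** The concern holds as an inconsistency between stated passages. The hypothesis and the power sentence are worded as a conjunction, while the alpha rule is built for two separate claims. The 80% is correct for each comparison and overstated if read as power for both weeks, by about 7 to 14 percentage points (79.5% against 72% to 66%) for correlations of 0.8 to 0.3. The size of the gap depends on that assumed correlation, on a true difference of zero and on equal attrition at both weeks; its direction does not depend on the correlation, for any value below 1. The documents do not show that the trial is underpowered for a rule it has adopted, nor that its type I error exceeds the declared level.

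**What to change.** 1. In Sample Size and Power, restate the figure along these lines: *80% power for each comparison; about 66–72% to show noninferiority at both weeks, assuming a correlation of 0.3–0.8 between the two test statistics.*
2. Make Hypothesis 1(a) and the Aim 1 analysis section agree on one success rule:
   - **(a) Separate claims.** Keep one-sided 0.025 per week and state that each week is its own claim, with no order imposed. The existing split already controls the error. Testing week 26 only after success at week 8 is not needed, and would lower the power for the week 26 claim from about 80% to the joint figure.
   - **(b) Both weeks required.** State that the hypothesis is supported only if both tests succeed. No split is then needed: one-sided 0.05 per week holds the declared overall 0.05 with about 78–82% joint power. Keeping 0.025 per week is stricter and gives the 66–72%.

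The cost is wording only, with a less favourable stated joint power. No additional participants are needed to make the text consistent.
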